#### Outcome measures: “quality of care” & “disease burden”

Quality of care refers to: (1) control rate, including the average personal BP/GLU control scores and population BP/GLU control rate; (2) cases of new complications per capita during intervention period; (3) re-admission rate within 30 days; (4) quality of treatment, including recovery rate, consistency rate of admission–and–discharge diagnosis, consistency rate of township–and–county hospital diagnosis, consistency of medication; (5) patient satisfaction rate.

Disease burden refers to: (1) QOL was measured by the Short Form Health Survey Questionnaire (SF-36)”; (2) average medication burden per chronic capita, measured by Standardized Drug Price Investigation.

#### Process measures: “patient behaviour” and “supplier behaviour”

Patient behaviours refer to: (1) population compliance rate, including compliance to medication and compliance to follow-ups; (2) lifestyle change rate, including less salt/fat/cigarette/alcohol, more exercise and stable emotion control; (3) patient awareness rate, including awareness of risk factors, complications and other seven questions of chronic disease knowledge; (4) self-efficacy rate, including patient efficacy of control their own behaviours.

Supplier behaviours refer to: (1) referrals, including emergency referrals, regular referrals and rehabilitation referrals; (2) communication intensity, including communication frequency between different clinicians and between clinician-and-primary caregivers; (3) the cases of unnecessary exams per capita; (4) the average referral time and waiting time; (4) staff satisfaction scores.

Besides, the index of continuous service rate refers to patient–and–supplier behaviour, which indicates the continuous contact of the same patient and primary caregivers. We use continuity of care index (COCI) to reflect the continuous contact of the same patient and primary caregivers, which is important index examining the possibility of high quality in primary care provision [32]:

In this calculation, *N* stands for the sample size, and *n* stands for different providers' number; and COCI reflects the dispersion of personal contacts. The COCI takes on values between 0 and 1. We assume that the continuous contact with the same primary caregivers will do most good for our patients, so a value of 1 signifies the situation when the same provider is seen at every visit, and 0 signifies when different providers are seen.

#### Structure measures: “system efficiency”

The system efficiency mostly refers to the compare relation of medical expenditure of county–to–township hospitals, including inpatient visits, in-patient fee, average length of stay, average cost per case, average exams per case and the average use of necessary medicine. And integration degree of MDT is measured by the Integration Degree Questionnaire evolved from D'Amour's collaboration typology model [33].

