There were four types of pathway. A-type was community treatment, treating patients in the village and township levels. Under this pathway, the patients with minor occasions might be cured by simple medication. Once the patients finished visits, he/she would just turn back home and there would be an in-door follow-up offered by the nearest village doctor within three days to make sure if he/she had recovered, if not, the management level would be upgraded and the patient would be transferred to a higher-level institution. This would save the inconvenience for the remote and old residents. B-type was emergency case, and C-type was complex/serious complications. Under either of these circumstances, once the village/township doctors found out such cases they had to contact with the corresponding county coordinator and transfer the patients to the relevant department. The cases were defined as: (1) instant BP ≥ 180/120 mm Hg/GLU ≥ 16.7 m mol/L; (2) severely damaged target organ; (3) and/or had other complications from cardiovascular, cerebrovascular and circulatory system. During the hospitalisation period, they should re-contact the county doctor to track the patients' status and follow-up after the patients were discharged. D-type was random entrance, including patients who were newly recognised or had a random entrance from outside of the pathway. Whenever it happened, the patients would be identified by their ID card and enrolled in MIP, and the doctor who discharged the patient must contact his/her neighbourhood doctor to establish a new file in the first place and start to follow-up (see Figure 4).

We made specific guidelines on how to assess and recruit the patient into the MIP based on complication diseases: coronary heart disease, stable angina, unstable angina, ST elevation acute myocardial infarction, non-ST elevation acute myocardial infarction, heart failure, arrhythmia, ketoacidosis, non-ketotic hyperosmolar syndrome, lactic acidosis, diabetic nephropathy, diabetic patients with cerebrovascular disease, diabetic ketoacidosis diabetic coma. In these pathways we pacifically pointed out what measurement the township physician should provide and what the county professionals should/should not do based on the first stage treatment.

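### Length of stay, cost and exams per case are averaged over admissions and hospital levels that the intervention is meant to change, so group differences in them mix case mix with performance

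*Protocol article*

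**What the plan says.** All places are in the Protocol article.

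- **Structure measures (system efficiency).** Efficiency is mainly the relation of county to township medical expenditure, "including inpatient visits, in-patient fee, average length of stay, average cost per case, average exams per case" and average use of necessary medicine.
- **Outcome measures (quality of care and disease burden).** The list has "re-admission rate within 30 days" and, under quality of treatment, the recovery rate. No hospital level is given for either. New complications are counted per capita.
- **Process measures.** One supplier outcome is "the cases of unnecessary exams per capita".
- **Multi-institutional clinical and management pathway.** For minor conditions, "A-type was community treatment, treating patients in the village and township levels". For emergency and complicated cases found by village or township doctors, "they had to contact with the corresponding county coordinator and transfer the patients to the relevant department".
- **System global budgets and pay-for-performance.** The team is paid in advance as a whole and may redistribute savings. The stated purpose includes moving attention towards primary care and avoiding unnecessary treatment. *Previous researches* concedes that pre-payment may reduce visits.
- **Statistical analysis.** The difference-in-differences model mainly includes group, time and their interaction. No severity or case-mix term is named.
- **Outcomes measures.** The primary outcomes are period BP/GLU control and drug compliance.

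**The concern.** Randomising towns makes the managed patients comparable between groups, within chance. It does not make the admitted patients comparable once the intervention has altered who is admitted and at which level. An average per admission then changes for two reasons: each kind of patient may be treated differently, and the mix of patients in the denominator may differ. Only the first is performance.

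Difference-in-differences does not separate the two. It removes stable group differences and time trends common to all groups. A change in case mix that the intervention causes, in the treated towns only and after the start, stays in the group-by-time term.

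System efficiency is one of the three effects the abstract expects and part of Assumption 1. The contrast between the two treatment groups (Assumption 2) is exposed as well, because payment is itself meant to influence what care is given and where.

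**Working it through.** The plan gives no admission counts, costs, stays or recovery rates, so there is no plan figure to reproduce. All inputs below are assumptions. The purpose is to see what the measures do when no patient is treated worse.

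**Assumed baseline, per 1,000 managed patients**
- County: 40 severe admissions (cost 10, stay 14 days, recovery 0.60) and 60 moderate (cost 5, stay 8 days, recovery 0.85).
- Township: 100 mild admissions (cost 1, stay 4 days, recovery 0.98).
- A moderate case treated in the township costs 3, with the same stay and recovery as in the county.

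**Formula.** Cost per case at a level = sum of (number × cost) ÷ number of admissions at that level. Baseline county: (40×10 + 60×5)/100 = 7.00.

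**Scenarios**
- A: 30 moderate cases move to the township.
- B: as A, and 25 mild admissions are avoided.
- C: 30 moderate county admissions are avoided altogether.

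| | County cost/case | Township cost/case | Ratio | Pooled cost/case | Total cost | County share |
|---|---|---|---|---|---|---|
| Baseline | 700/100 = 7.00 | 100/100 = 1.00 | 7.00 | 800/200 = 4.00 | 800 | 87.5% |
| A | 550/70 = 7.86 | 190/130 = 1.46 | 5.38 | 740/200 = 3.70 | 740 | 74.3% |
| B | 550/70 = 7.86 | 165/105 = 1.57 | 5.00 | 715/175 = 4.09 | 715 | 76.9% |
| C | 550/70 = 7.86 | 100/100 = 1.00 | 7.86 | 650/170 = 3.82 | 650 | 84.6% |

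Total cost falls in every scenario. Cost per case does not follow it:
- The county-to-township ratio falls in A and B and rises in C, although C is the cheapest.
- Pooled cost per case falls in A and rises in B, although B costs less than A.

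**Stay and recovery in scenario B**
- County stay: 1,040/100 = 10.4 days becomes 800/70 = 11.4. Township stay: 4.0 becomes 540/105 = 5.1. Pooled: 1,440/200 = 7.2 becomes 1,340/175 = 7.7. Total inpatient days nevertheless fall from 1,440 to 1,340.
- County recovery: 75/100 = 75.0% becomes 49.5/70 = 70.7%. Township: 98.0% becomes 99/105 = 94.3%. Pooled: 173/200 = 86.5% becomes 148.5/175 = 84.9%. No patient's own chance of recovery has changed.

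In scenario A, pooled stay and recovery do not change (7.2 days, 86.5%).

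**Range.** With 15 to 45 moderate cases moved and 0 to 50 mild admissions avoided, total cost is 660 to 770, always below 800. County cost per case is 7.35 to 8.64, township 1.26 to 1.95, and pooled 3.55 to 4.80 on either side of 4.00.

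**30-day re-admission, separate assumed figures.** Take 60 mild admissions (4% re-admitted) and 40 severe (15%): (2.4 + 6.0)/100 = 8.4%.
- If 30 mild admissions no longer occur: (1.2 + 6.0)/70 = 10.3%, while the number re-admitted falls from 8.4 to 7.2.
- If those 30 are admitted in the township instead and both levels are counted: (1.2 + 6.0 + 1.2)/100 = 8.4%, unchanged.

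**The case against.** A reader might infer that the efficiency question will be answered backwards, with good triage showing up as worse results. The documents do not support that.

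- **Not every efficiency item is per case.** The sentence opens with county-to-township expenditure. Inpatient visits are a volume, and the in-patient fee may be a total. In the scenarios above, county admissions and county spending fall as intended. A wrong conclusion would need the averages to be read alone. This stands.
- **The direction is not fixed.** The scenarios move cost per case both ways. The abstract also expects better risk-factor control. If that reduced severe admissions, the county mix could become milder. This stands.
- **No county-to-township comparison is stated for re-admission or recovery.** The rise to 10.3% appears only if admissions drop out of the denominator, either because they are avoided or because the rate is confined to the county. This stands, but both rates still exist only for admitted patients.
- **Definitions may be sharper elsewhere.** Table 5 is not reproduced, and the model only mainly includes three terms, so case-mix terms are not excluded. This stands in part. The text itself states averages per case, and adjusting for severity among the admitted does not restore the comparison of randomised groups.
- **The change is not free.** The article describes reimbursement only for in-patient expenditure. Nothing shows that village or out-patient costs are in the insurance extract. This stands and limits the fix.

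**Conclusion.** The point holds in a limited form. Average length of stay, cost per case and exams per case are conditional on admission and hospital level, which the intervention is designed to change after randomisation. Group differences in them, and in their county-to-township relation, cannot be read as efficiency alone. Re-admission and recovery rates share the conditioning on admission only.

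Neither the size nor the sign of the distortion can be derived from the documents. The figures above show what can happen under assumed inputs and are not a forecast. The conclusion takes a case to be an inpatient admission, as the items around it suggest.

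The primary outcomes, inpatient visits, the in-patient fee if it is a total, and the per-capita outcomes are untouched. This is a weakness in secondary measures that is worth correcting, not a threat to the trial's main result.

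**What to change.** In *Structure measures* and *Outcome measures*, base the between-group comparison on these quantities per sampled managed patient per year, with zeros included and county and township hospitals combined:
- admissions;
- inpatient days;
- inpatient cost;
- 30-day re-admissions;
- inpatient exams, if they can be linked to patients.

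Add the county share of total inpatient cost, which shows the shift between levels directly. Keep the per-case averages as descriptive figures, read beside admission volumes.

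The main ingredients are in place. The sampled patients are a fixed cohort without replacement (*Enrollment and masking*), all must be consistently enrolled in the insurance scheme (*The inclusion criteria*), and reimbursement data are extracted from the local electronic system (*Project costing*).

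The cost is some data linkage and programming. There is also a limit: care moved to out-patient or village level is counted only if the insurance extract or the follow-up files hold it. Otherwise moved care would look free and favour the intervention. Label the per-patient totals as inpatient only unless that coverage is confirmed.

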#### Project costing

To make an economic evaluation of the policy trial to compare with the usual care model, we also take records of the extra expenditures of project such as publicity, training, patient ID card production, printing, transportation, meeting organisation, consumables and accommodation. Besides, the increased staff workload is also recorded into counting the cost by adding the working hours into cash under the National Labor Payment Standard and the average local salary. The team coordinators were asked to take a monthly record of all the actual expenditures and increased working hours.

All data were collected through structured patient questionnaire, staff questionnaire, institution investigation, follow-up files, medical records and the reimbursement data that extracted from the local electronic insurance system (see Table 5).

### Analysis strategy

#### Statistical analysis

There are two-stage analyses in this trial. First, we will use difference-in-differences (DID) model [34] to examine the effects of the intervention; second we will use structural equation modelling (SEM) [35] to explore the hidden effecting pathway of how the intervention works.

The DID model is often used to exclude out the time effect and group differences. In the pilot study, we had mimicked the regression tendency of BP falling to ensure a similar time effect in groups. In the main study, we mainly include three explanatory variables in the regression model: group, time and interaction term between group and time. And to exclude the intra-cluster correlation (ICC) from non-independent clustering and cross-level interaction, we choose three-level regression model to control for the potential confounders of the context effect. For other repeatedly measured outcomes like BP control, lifestyle changes and professional behaviours we mainly use three-level and repeated measure multivariate analysis of variance to examine the group differences. The three levels we consider are: level 1 – individual, level 2 – cluster/village, level 3 – group. Data analysis will be carried out on the Stata (IC: 13.1). In SEM we hope to establish an explainable relationship between intervention effect of health outcome and design effect of payment system reform.

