### Sampling and randomisation

Six towns were selected randomly from the 24 rural communities and then were categorised into three groups with a combined consideration of population size, social development and distance. Because there were obvious potential confounders in social experiment, the towns were first categorised into two types based on comprehensive consideration of socio-economic development level and hospital ability, two basic confounders which we assumed high relevance with the intervention outcome. The socio-economic development level mainly indicated the patient population, their per capita income and average distance from the location to downtown (translated into traffic time by public transportation). The hospital ability represented resource possession and staff skills. Second, every two towns of each type were randomly assigned into treatment/control groups to ensure group comparability. These two steps were done to make sure towns comparable both within groups and within cluster types in case of different comparison need.

In patient sampling, we used three-stage stratified random sampling strategy instead of propensity scoring matching, concerning the complexity of sampling and excessive workload. We chose gender, age and risk level as the three stratify factors. Risk level was a comprehensive factor that summing up the BP/GLU level as well as the possible risky factors due to the patient lifestyle. The hypertension and diabetes II patients were divided into three and two risking groups before the baseline, and we stratified the patient library mainly in accordance with the original files but with a slight alternation based on professional re-assessment after personal contact at the baseline.

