## Discussion

This is the first trial in both developing countries and rural areas to gather evidence of health policy reform on delivery and payment system integration using experimental design. Previous studies on chronic disease management mostly focused on clinical and technical novelties, and did not develop inter-systems vision and strategy when reforming the delivery system [36, 37]. Although there were researches which had already proved the importance of simultaneous payment system intervention on changing delivery system [38–40], we still do not know in what way and to what extent can it affect the health outcomes. Thus, through this trail we first hope to build a feasible policy package to help health system integration, and then we want to identify the barriers and facilitators during implementation of professional/organisational collaboration on community chronic disease management. By doing this, we especially expect to prove the importance of integrated and systematic thinking when making decisions of health policies. The outputs will be an integrated care model of community-based chronic disease control, including policy packages of clinical guidelines, team guideline and financial stimulation plan. With the fundamental environment analysis we hope this model can be generalised to or at least give some hints to other LMICs/rural areas which are facing with similar problems.

The trial design has some potential limitations. Initially, we were going to use randomised controlled trial which may provide the highest level of evidence even in social science experiment as many previous studies in China succeeded to [41–43]. However, the intervention strategies we designed in this trial will not succeed without the acknowledgement in each cluster, which means the randomisation process might sacrifice a little. As a result, the proof power may be reduced. To compensate, we controlled the potential contextual and individual confounders during the grouping and sampling period to achieve a maximum control of cases. Second, though a latest systematic review pointed out that there was no evidence to prove that the multifaceted interventions were more effective in changing the health care professionals' behaviours [44], still several experiments had shown better effects of multifaceted interventions on hypertension and diabetes II patients [45–47].

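### The stated DID model leaves out gender, age and baseline risk level, the recorded factors used to stratify patient sampling; the loss is mainly precision, and town type belongs in a sensitivity analysis

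*Protocol article*

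**What the plan says.** In the Protocol article, Statistical analysis, the DID model is described by its terms: "we mainly include three explanatory variables in the regression model: group, time and interaction term between group and time". The same paragraph adds that "we choose three-level regression model to control for the potential confounders of the context effect", and defines the hierarchy: "The three levels we consider are: level 1 – individual, level 2 – cluster/village, level 3 – group". BP control, lifestyle change and professional behaviour are listed among the other repeatedly measured outcomes, to be analysed mainly by three-level and repeated-measures multivariate analysis of variance.

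Sampling and randomisation describes two sets of design factors.

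- **Towns:** "the towns were first categorised into two types based on comprehensive consideration of socio-economic development level and hospital ability". These are called "two basic confounders which we assumed high relevance with the intervention outcome". Then "every two towns of each type were randomly assigned into treatment/control groups to ensure group comparability".
- **Patients:** "We chose gender, age and risk level as the three stratify factors". Risk level combines BP/GLU level with lifestyle risk factors. It has three groups for hypertension and two for type 2 diabetes, and was slightly revised at baseline.

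The Discussion concedes that randomisation may be weakened and says that, to compensate, "we controlled the potential contextual and individual confounders during the grouping and sampling period". No section names town type, gender, age or risk level as a term in any model.

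**The concern.** The design treats these factors as important enough to stratify on, and calls the two behind town type confounders, yet the named model terms include none of them. The three-level structure does not fill the gap, because its levels are individual, village and group. Neither town nor town type is among them.

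Two things are at stake. First, if change over time depends on gender, age or risk level, that variation stays in the error term and the group×time estimate is less precise than the data allow. Second, the patient sample is a closed cohort with a planned 20% drop-out and no replacement. Strata that start balanced can end unbalanced, and a model without stratum×time terms then has no protection against it. Risk level is the factor most likely to predict change, since it is partly built from BP/GLU.

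**Working it through.** **The plan's own figure.** The article gives no precision figure for the DID model. Its only reproducible power statement (note to Table 2: over 80% for a 0.20 difference with 120/96 or 120/120 cases) is an individual-level two-proportion calculation. At two-sided 0.05 it gives 0.837–0.853 and 0.877–0.890, so it reproduces, but it says nothing about covariates.

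**Step 1: what cancels.** Write the outcome of patient i at time t as fixed traits × β, plus time, plus group×time. In a linear model on patients measured twice, the change is free of β. Adding gender, age, risk level or town type as main effects only would leave the group×time estimate as it is. Only stratum×time terms can alter it or its standard error (SE).

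**Step 2: precision from the patient factors (assumed inputs).** Take patient SD of change 1, village SD 0.1, and two groups each of 20 villages with 16 patients.

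- Variance of a village mean: 1/16 + 0.01 = 0.0725.
- Variance of the group difference: 0.0725 × (1/20 + 1/20) = 0.00725, so SE = 0.085.
- If the factors explain a share R² of the patient variance, 1/16 becomes (1 − R²)/16.
- Town variance, with two towns per group, adds SD² × (1/2 + 1/2) to the group-difference variance.

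| Town SD | Variance, no covariates | R² = 0.10 | R² = 0.20 | Fall in SE |
|---|---|---|---|---|
| 0 | 0.00725 | 0.006625 | 0.00600 | 4% to 9% |
| 0.1 | 0.01725 | 0.016625 | 0.01600 | 2% to 4% |
| 0.2 | 0.04725 | 0.046625 | 0.04600 | about 1% |

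Example, first row: √(0.00600/0.00725) = 0.91. The gain shrinks as town variance grows.

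**Step 3: when bias appears.** Bias = (difference between groups in stratum share) × (difference between strata in change). With no imbalance it is zero. With an assumed 10-point imbalance in high-risk share and an assumed 20-point difference in change in BP control, it is 0.10 × 0.20 = 0.02, or 2 points. Halving both gives 0.5 points. The documents supply neither input.

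**Step 4: town type, simulated.** Two groups, two types, 10 villages per town, same SDs, 2,000 runs:

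| Setting | Without type: bias, model SE, type I error | With type×time: bias, model SE, type I error |
|---|---|---|
| No type trend | 0.00, 0.085, 5.6% | 0.00, 0.085, 5.7% |
| Type trend 0.3 SD, balanced | 0.00, 0.097, 2.4% | 0.00, 0.084, 5.0% |
| Same trend, 50% more type B patients per village in one group | 0.03, 0.094, 3.6% | 0.00, 0.081, 5.0% |
| Trend 0.3, town SD 0.1 | 0.00, 0.100, 12.8% | 0.00, 0.086, 17.3% |
| No trend, town SD 0.1 | 0.00, 0.087, 17.8% | 0.00, 0.086, 18.7% |
| Trend 0.3, town SD 0.2 | −0.01, 0.106, 31.9% | −0.01, 0.090, 38.5% |

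Row 3 checks by hand: the type B share is 24/40 = 0.6 against 0.5, and 0.1 × 0.3 = 0.03.

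So balanced types give no bias, only a conservative SE. Where towns truly vary and town is not modelled, adding type makes an already inflated type I error worse.

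**Step 5: degrees of freedom at town level.** Six towns − three groups = 3. With type, 2. The critical t goes from 3.18 to 4.30 (ratio 1.35). To break even, type would have to cut the residual town-level SD to 3.18/4.30 = 0.74 of its value, which is a cut in variance of 1 − 0.74² = 45%.

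**The case against.** A reader might infer that the trial admits weak randomisation, names its confounders and then leaves them uncontrolled. The documents do not support that, for these reasons:

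- The Discussion claims control through grouping and sampling, that is by design. Allocation within type, read as one town of each type per group, balances type across the three groups.
- The article says a pilot exercise on falling BP was meant to secure a similar time effect in the groups. It does not describe a check by risk level, and a pilot in the second half of 2012 cannot guarantee equal trends over 24 months from June 2013. It is nevertheless the plan's stated answer to differing trends.
- The sampling fractions are not stated and the content of Table 4 is not visible, so a difference in risk mix between groups is conjecture. The article also plans to test the samples for differences at baseline and end-line.
- The BP outcome is a period control rate over repeated readings, which dampens regression to the mean compared with one entry reading.

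The strongest procedural objection is the word *mainly*: the list of terms is not closed, and a covariate list may stand in a plan not shown. That lowers confidence that the factors will really be left out. It does not remove the point, because the article does state the model, and naming recorded baseline factors in it is a concrete improvement.

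One caveat runs the other way. Cancellation of main effects is exact only on a linear scale. Drug compliance is a proportion, and the article does not say on which scale its DID will be fitted.

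**Conclusion.** The stated DID model does not use gender, age and baseline risk level, although the trial stratified on them and records them. The consequence is mainly lost precision: 4–9% in the SE if they explain 10–20% of the patient-level variance in change and towns do not vary, down to about 1% at a town SD of 0.2. There is also missing protection against chance or drop-out imbalance in factors that predict change. All these inputs are assumed. Uncontrolled confounding is not established, and the 2-point bias is an illustration, not an estimate.

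For town type the case is a trade-off. Including it matches the stratified allocation and corrects a conservative SE when trends differ by type. It also costs one of three town-level degrees of freedom and, while town is left out of the model, raises simulated type I error from 13–32% to 17–39%. It is better shown beside the primary result.

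The larger fault in the same paragraph is separate: town, the allocated unit, is not a level, while group is both an explanatory variable and the top level. Adding covariates does not cure that.

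**What to change.** In the Statistical analysis section:

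1. Prespecify gender, age and baseline risk level, each with its interaction with time, as covariates in the primary DID models. Use the same covariates in the corresponding repeated-measures models for BP control.
2. Fix the coding beforehand: the form of age, and the risk level as it stood after the baseline re-assessment, coded separately for hypertension (three groups) and diabetes (two groups).
3. Report a type-stratified result (town type and type×time) as a sensitivity analysis, not as the primary model.

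**Cost.** A change of wording, made before the analysis; no new data. With linear age, the interactions use 1 + 1 + 2 = 4 patient-level terms against 1641 hypertension patients, and 1 + 1 + 1 = 3 against 332 diabetes patients. The sensitivity analysis will be imprecise with six towns (critical t 4.30 at two degrees of freedom) and should be read as a check on direction. The missing town level needs its own correction.
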